### Recruitment and Retention Strategies

Active and passive recruitment strategies will be used to recruit individuals with CLBP include (1) contacting CLBP participants enrolled in an institutional review board (IRB)–approved pain registry, (2) advertisements on social media (Instagram, Facebook, Twitter, Reddit, and Craigslist), (3) placing printed advertisements in public transportation vehicles and local newspapers, and (4) distributing flyers at local outpatient clinical sites and local universities. We will recruit continuously and start a new cohort every 6 months, so that there will be cohorts in both interventions and follow-up phases throughout the study. This approach will help control for seasonal effects and other potential confounds. All participants will receive a yoga or exercise mat, block, and strap prior to their first session, and US $70 following the baseline, 6- and 12-week postintervention, and 3- and 6-month follow-up assessments with an additional US $50 for those who complete all data collection sessions.

Interested volunteers are asked to complete a web-based screening questionnaire via REDCap (Research Electronic Data Capture; Vanderbilt University), which includes questions to ensure they meet inclusion and exclusion criteria and can participate safely. Volunteers who are deemed eligible to participate are contacted by study staff to schedule their baseline appointment.

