#### Interventions

All yoga and stretching and strengthening sessions will take place on a secure web-based platform. This delivery modality will provide more inclusive participation and reduce barriers such as participant transportation and parking. For both study arms, 75-minute classes will be offered 3 times per week for 12 weeks. Participants will be asked to attend at least 2 out of 3 of the offered classes per week. The importance of attending 2 sessions per week is emphasized during the first session and throughout all subsequent sessions. Participants who repeatedly miss sessions without notifying the study personnel will be contacted to check on the reason for nonattendance and to encourage resuming participation as soon as possible. Participants are encouraged to consult with the instructor individually before or after class about problems or difficulties they are encountering at home or in the formal sessions.

Participants are asked to practice exercises at home on days they do not attend formal synchronous sessions to maximize the benefit of the intervention. Participants will be emailed daily links to prerecorded practice videos that are approximately 25 minutes in length and asked to record the amount of time they spent on the practice videos.

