### Statistical Analysis

The primary aim of this study will test the null hypothesis that the 2 population means are equal between the yoga and stretching and strengthening groups on the primary outcome, pain severity as measured by the BPI-SF, as well as the primary MOA, ER as assessed by the DERS. Power calculations incorporated prior effect sizes from works by others. A proposed sample size of 102 per group, which adjusted for attrition, was calculated to detect statistically significant results with 80% power (estimated *d*=0.50). In consideration of our secondary aims, we also powered the detection of paths a and b within pain interference mediation models. This was done using simulation in R (R Foundation for Statistical Computing; N=5000). Following simulation methods (N=5000) presented in Fritz and MacKinnon [76], sample size was determined by increasing simulation sample size until 90% of simulations significantly detected both paths a and b with estimated effect size magnitudes of *d*=0.39 (path a) and *d*=0.26 (path b) at α=.05. A proposed sample size of 116 was calculated, which was already reached when powering our primary aim.

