### Data Analysis

All analyses will be performed in SPSS (version 29; IBM Corp). A *P* value of .05 or less will be considered statistically significant. The primary outcome is pain severity (BPI-SF) and the primary MOA is ER (DERS). We will examine baseline demographics and study variables descriptively and test for differences between yoga and stretching and strengthening groups. If assumptions are met, a series of 2-sided *t* tests, mixed effects models, and path analyses will test our hypotheses. A mediation path analysis will be conducted examining the indirect path of group and change in ER from baseline to 6 weeks (path a), and change in ER from baseline to 6 weeks and pain severity (BPI-SF) at 12 weeks (path b) controlling for baseline pain severity. The magnitude of indirect path b will be assessed controlling for path a and the direct path between group and change in pain severity at 12 weeks (path c) to test if changes in ER predict subsequent changes in pain severity. Identical models will be created with change in ER from baseline to 12 weeks and pain severity at 3- and 6-month follow-ups. The magnitude of indirect path b will be compared between groups to test if the path between ER and pain severity is greater in the yoga group than in the stretching and strengthening group. If 95% CIs of path estimates do not contain 0, they will be considered meaningful. Finally, a series of moderated mediation path analyses will be conducted, examining the measures of baseline pain sensitivity (QST scores and normalized gene expression values), strength and flexibility, pain interference, and quality of life as moderators of the identical mediation model. All analyses will also be adjusted for important covariates including, but not limited to demographics (eg, biological sex, race, and sex), cohort, instructor, and intervention components (Essential Properties of Yoga Questionnaire) and credibility or perception of success (Credibility Expectancy Questionnaire). Sensitivity analyses will examine whether treatment responders and nonresponders differ significantly in baseline ER abilities. Baseline DERS scores will also be examined as a continuous moderator in main study analyses to establish whether some individuals may enjoy greater benefit from this intervention more than others.

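### Clustering by group class is not allowed for in the sample size, and adjusting for cohort and instructor as covariates does not deal with it

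*Protocol article*

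**What the plan says.** The Protocol article describes individual randomization stratified by sex (Randomization and Blinding), followed by group delivery in both arms (Abstract, Methods).

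- **Cohorts** (Recruitment and Retention Strategies): "We will recruit continuously and start a new cohort every 6 months".
- **Classes** (Interventions): "For both study arms, 75-minute classes will be offered 3 times per week for 12 weeks". Participants are asked to attend at least two of the three.
- **Instructors:** registered yoga teachers lead the yoga arm. Physical therapists or other exercise instructors lead the control arm.
- **Sample size** (Statistical Analysis): "A proposed sample size of 102 per group, which adjusted for attrition, was calculated to detect statistically significant results with 80% power", with "estimated *d*=0.50". A separate simulation for the mediation paths gives 116. Neither calculation mentions an ICC, a class size or a design effect.
- **Tests** (Data Analysis): "a series of 2-sided *t* tests, mixed effects models, and path analyses will test our hypotheses", and "A *P* value of .05 or less will be considered statistically significant".
- **Adjustment** (Data Analysis): all analyses are to be "adjusted for important covariates including, but not limited to demographics (eg, biological sex, race, and sex), cohort, instructor", followed by further items. Neither cohort nor instructor is given any other role.

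**The concern.** People in the same arm of the same cohort share classmates, a calendar period and a pool of instructors. Their outcomes may therefore be correlated. Any variation between such classes is part of the error of the yoga-versus-control contrast. An analysis that omits it gives intervals that are too narrow for pain severity, for the Difficulties in Emotion Regulation Scale (DERS) and for path a (group to change in emotion regulation). The plan treats a path estimate as meaningful when its 95% interval excludes zero, so intervals that are too narrow would lead directly to false claims about mechanism.

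The article does more than leave this open, because it assigns cohort and instructor a role as covariates. That role has two separate problems:

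- **Cohort:** a cohort term removes only what both arms of a cohort have in common. Differences between the yoga class and the control class of one cohort remain in the error.
- **Instructor:** if each instructor teaches in one arm only, fixed instructor terms together determine arm. This is a problem of estimability, not of standard errors, and it does not depend on any ICC.

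**Working it through.** **1. The plan's own figure.** With d = 0.50, two-sided α = 0.05, 80% power and independent participants, a t test needs 64 evaluable per arm. The plan has 102. The ratio 64/102 = 0.627 corresponds to about 37% attrition. The attrition rate is not stated, so 102 cannot be confirmed.

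**2. Class size (assumed).** Enrolment was 138 between September 2020 and January 2024, about 40 months or about 7 six-monthly cohorts. That is 138/7 ≈ 20 per cohort, or about 10 per arm. At full enrolment with 8 cohorts it is 102/8 = 12.75 per arm per cohort. The cluster is taken to be one arm of one cohort. The article gives no ICC, so a range is shown.

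**3. Type I error of a test that ignores class.** DEFF = 1 + (m − 1) × ICC, and actual α = 2 × [1 − Φ(1.96/√DEFF)].

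| ICC | DEFF, m = 10 | actual α | DEFF, m = 12.75 | actual α |
|---|---|---|---|---|
| 0.01 | 1.09 | 0.061 | 1.12 | 0.064 |
| 0.02 | 1.18 | 0.071 | 1.24 | 0.078 |
| 0.05 | 1.45 | 0.104 | 1.59 | 0.120 |
| 0.10 | 1.90 | 0.155 | 2.18 | 0.184 |

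**4. Does cohort adjustment cure it?** Simulated type I error, 10,000 runs per setting, 8 classes of 13 per arm:

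| class-level ICC | t test | regression with fixed cohort | t test on class means |
|---|---|---|---|
| 0 | 0.051 | 0.051 | 0.052 |
| 0.01 | 0.064 | 0.063 | 0.050 |
| 0.02 | 0.079 | 0.080 | 0.051 |
| 0.05 | 0.120 | 0.124 | 0.050 |
| 0.10 | 0.184 | 0.194 | 0.049 |

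The cohort term gives no protection against class-level variation. When the clustering (ICC 0.05) was wholly shared by both arms of a cohort, there was no inflation: 0.048 for the t test and 0.053 with cohort adjustment.

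**5. Instructor.** Take four instructors, two in each arm. The matrix of instructor indicators has rank 4, and adding the arm column leaves it at 4. Arm is then a linear combination of the instructor terms, and its effect cannot be estimated.

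**6. Power at d = 0.50**, 8 classes per arm, normal approximation with n/DEFF and m = n/8:

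| evaluable per arm | ICC 0.01 | 0.02 | 0.05 | 0.10 |
|---|---|---|---|---|
| 102 (no loss) | 92% | 90% | 81% | 68% |
| 82 (20% loss, assumed) | 87% | 84% | 75% | 64% |
| 64 (37% loss) | 78% | 76% | 68% | 58% |

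These figures ignore the loss of degrees of freedom from having few classes, so they are somewhat optimistic. The room between 64 and 102 would absorb a design effect of 102/64 = 1.59 with no attrition, or 102 × 0.78/64 = 1.24 with 22% attrition.

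**The case against.** The strongest reply is that the article does not show that every analysis ignores class. It names mixed effects models alongside t tests and path analyses and does not give their random terms. A condensed article may leave those to the full plan. It also names no single primary test, so it would be wrong to say that the primary test is a t test. This stands. The point reaches the t tests and path models, and any mixed model without a class term. It does not remove the concern, because the only stated handling of cohort and instructor is covariate adjustment.

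A second reply is that class-level correlation may be small. Delivery is web-based and manualized, fidelity is rated weekly, home practice uses recorded videos, and nothing says that one instructor serves a whole class. This also stands as a reason to doubt the upper end of the ICC range. It is no reason to expect exactly zero.

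A reader might infer that the quoted 80% power is overstated. The documents do not support that. About 64 evaluable per arm suffice under independence, 102 are planned and the attrition rate is unknown. At ICC 0.02 with 20% loss, power is about 84%. Spare sample can offset lost power, but it does not correct the type I error or the coverage of intervals.

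Finally, aliasing requires that nobody teaches both arms. The different instructor types suggest this, but the article does not state it.

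**Conclusion.** The point holds in conditional form. Treatment is delivered in groups, the sample size has no stated allowance for clustering, and covariate adjustment for cohort does not remove variation between classes. If the class-level ICC is above zero, t tests and path models without a class term have type I error above 5%. With 10 to 13 per class, it is about 6% at ICC 0.01 and 16-18% at 0.10. Class size and ICC are assumptions. Without a class-level ICC from the documents, it cannot be said that the error rate will in fact exceed 5%, and at zero ICC or with purely cohort-wide clustering it would not.

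The instructor problem is distinct. If instructors do not cross arms, a fixed instructor term makes the arm effect inestimable, whatever the ICC. A loss of power below 80% remains possible but is not shown.

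**What to change.** - **Pain severity, DERS and path a:** use a mixed model with a random intercept for class (cohort-by-arm), cohort as a fixed effect, and small-sample degrees of freedom such as Kenward-Roger.
- **Instructor:** do not enter it as a fixed covariate. If it is modelled, use a random effect nested in arm.
- **Path models:** use inference clustered by class with a small-sample correction. The correction matters: with 8 classes per arm, uncorrected options still give about 8% (usual cluster-robust errors with a normal reference) or 9% (percentile cluster bootstrap).
- **Sample size:** state the assumed attrition, and show power over a stated range of ICCs with the design effect.

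No new data are needed beyond a record of class and instructor. The cost is wider intervals and fewer degrees of freedom, with only about 16-18 classes (assumed). With 8 cohorts, 16 classes less 8 cohort terms and 1 arm term leave as few as 7 degrees of freedom for the arm contrast. The power statement may also become less favourable.

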### Objectives

To address this gap, we will test the impact of a yoga intervention on ER and pain severity and functioning compared to a general stretching or strengthening intervention. This design allows us to isolate the additional effects of yoga above and beyond more general movement practices, thereby testing ER as a key MOA underlying the clinical effects of yoga on CLBP. Specifically, we will test whether yoga’s effects on CLBP (improved pain severity and interference) are mediated by improved ER, the extent to which effects are related to specific aspects of ER, and the role of pain sensitization as a mediator or moderator of effects.

For the active comparison intervention, we chose to use stretching and strengthening exercises, given that we are interested in determining not only whether yoga influences ER but also the extent to which these effects are due to aspects of yoga above and beyond nonspecific factors (eg, expectancies, time, attention, and effort) [13] as well as improvements in strength and flexibility [4]. The 2 intervention groups will be similar in many aspects, but only yoga will incorporate aspects that we hypothesize will facilitate ER (eg, breathwork, mindfulness, and relaxation). We selected the hypothesized MOA based on our extensive work regarding the therapeutic characteristics of yoga and mechanisms of CLBP [5,14]. Our 3-month and 6-month follow-ups will allow us to examine whether the effects of yoga emerge later or persist. The study is highly innovative in its approach to testing the MOA of yoga for alleviating CLBP. By identifying the specific mechanisms through which yoga may influence pain, these results will facilitate optimizing interventions to improve therapeutic accuracy for prescribing and using yoga for CLBP, a highly prevalent and costly health condition in the United States and worldwide.

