#### Yoga Intervention

##### Overview

The yoga intervention will be led by certified 500-hour registered yoga teachers trained in working with patients with back pain. The yoga for CLBP protocol [55] consists of classical hatha yoga with influences from vinyasa and Iyengar yoga. These yoga styles are those most commonly offered in clinical and community settings and emphasize the importance of modifications and adaptations including the use of props such as straps and blocks to minimize the risk of injury and make the poses accessible to people with health problems and limitations [56]. The manual developed to standardize the yoga classes offered in the intervention contains pictures and a description of how to perform each pose. The manual also includes suggested instructor dialogue, which may be paraphrased or varied slightly yet promotes consistent delivery, which enhances the replicability and generalization of results. The intervention includes some poses that could aggravate back conditions in some people if they are not modified; therefore, multiple modifications are suggested, and many poses are only worked up to after weeks of practice and individual attention from the instructor. The more challenging poses are never included in the home practice videos.

For each yoga class in the protocol, the instructor leads participants through a series of 23 yoga poses (32 total variations) at a slow-moderate pace. During the formal sessions, participants are instructed to take slow deep breaths, timing their inhales and their exhales with specific phases of poses. Participants are encouraged to emulate optimal alignment as demonstrated by the instructor and to focus on a goal or positive direction for their yoga practice. Yoga classes are constructed to allow optimal flow from one pose to another. Each session begins with a few minutes of deep breathing and mindfulness or meditation followed by 15 minutes of basic postures (poses 1-8) to warm up muscles by increasing circulation to provide increased flexibility as the class progresses. Most poses are conducted once per side. After the warm up, the instructor leads participants through a series of standing poses (poses 9-14) for 15 minutes. After the standing poses, the class moves into floor poses (poses 15-23) for 20 minutes. Sessions end with 5-7 minutes of complete relaxation in the standard ending pose “savasana,” during which additional positive affirmations are provided.

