##### Stretching and Strengthening Control Intervention

This intervention is designed to require a similar amount of physical exertion (stretching and strengthening exercises only, with no extreme movement). Classes will be led by physical therapists or other skilled therapeutic exercise instructors and involve conventional exercises appropriate for patients with CLBP, including a comprehensive set of exercises that stretch all the major muscle groups, with an emphasis on the trunk and legs. The intervention will include 12 stretching exercises used in the exercise arm of previous studies that have successfully compared exercise to yoga [57,58] (ie, gastrocnemius, soleus, quadriceps, posterior and inferior shoulder, upper trapezius, hip flexor, back extension, back rotation, hamstrings, hip external rotators, and back flexion). It will also include 3 additional stretches (hip internal rotators, hip adductors, and hip flexion). Each stretch will be held for approximately 60 seconds and repeated once. In addition to a complete set of full-body stretches, the class will begin with a 5-minute warm up period consisting of basic aerobics steps (ie, 1 minute each of walking in place, marching, lateral shuffling, turning and reaching, and box step) and will also include 4 exercises that strengthen the back, abdomen, and hips (ie, squats, crunches, oblique crunches, and back extensions). Over the 12 weeks, the repetitions of each strength exercise are increased from 8 to 30. Specific strength exercises are practiced in separate sets of 5 to 10 repetitions.

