### Exploratory Variables

Demographics, class attendance or home practice, expectancies, and substance use will be measured to examine the impact on the primary and secondary outcomes. A brief questionnaire (minimum data set as recommended by the National Institutes of Health Taskforce on Research Standards for CLBP) [54] will assess demographics (age, gender, race or ethnicity, education, and employment status) and medical or psychiatric history (comorbidities, medication usage, and ongoing treatments). Attendance at yoga or stretching sessions will be assessed using attendance data from the session recordings. The Essential Properties of Yoga Questionnaire [72] will be used to rate both interventions (yoga and stretching or strengthening) and measures the extent to which 14 different dimensions are emphasized in a mind-body intervention (eg, physical challenge, breathwork, restorative postures, and mindfulness). The Credibility Expectancy Questionnaire [73], a 6-item self-report instrument, will be used to assess treatment credibility and patient expectancy for improvement [74]. In order to assess participants’ use of tobacco, alcohol, prescription medicines, cannabis, and other nonprescribed substances, the Alcohol, Smoking, and Substance Involvement Screening Test [75] will be administered by study staff at each time point.

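### The covariate list for all analyses includes yoga-content ratings and instructor, which can make the adjusted yoga-versus-stretching effect inestimable or condition it away

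*Protocol article*

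**What the plan says.** The Data Analysis section sets the scope: "All analyses will also be adjusted for important covariates including, but not limited to demographics". The list continues with "cohort, instructor, and intervention components (Essential Properties of Yoga Questionnaire) and credibility or perception of success (Credibility Expectancy Questionnaire". No model is exempted.

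Four other places in the protocol article bear on this:

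- Exploratory Variables says that the yoga questionnaire "will be used to rate both interventions (yoga and stretching or strengthening) and measures the extent to which 14 different dimensions are emphasized". Breathwork and mindfulness are among the examples given.
- Objectives describes the intended contrast: "only yoga will incorporate aspects that we hypothesize will facilitate ER (eg, breathwork, mindfulness, and relaxation".
- The Overview under Yoga Intervention says who teaches yoga: "The yoga intervention will be led by certified 500-hour registered yoga teachers".
- Stretching and Strengthening Control Intervention says who teaches the control: "Classes will be led by physical therapists or other skilled therapeutic exercise instructors".

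The primary aim, in Statistical Analysis, is the difference between the two arms in mean pain severity (BPI-SF) and in emotion regulation (DERS).

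**The concern.** Covariates in a randomised comparison should be fixed before treatment can affect them. The yoga ratings are not: they score what was delivered after randomisation, on the very features meant to distinguish yoga from stretching. Adjusting for them asks what yoga does once its yoga content is held equal, which is not the trial's question.

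Instructor raises a different problem. If each instructor teaches in one arm only, knowing the instructor means knowing the arm, and a model with fixed instructor effects has nothing left from which to estimate arm.

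The coefficients at stake are the adjusted arm effects on BPI-SF severity and DERS, path a (arm to change in emotion regulation) and the direct path. The indirect effect is exposed too, because it contains path a.

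**Working it through.** **Inputs.** From Statistical Analysis: d = 0.50, 80% power, 102 per arm after an attrition allowance whose rate is not given. From Data Analysis: significance level 0.05, two-sided t tests. Assumed here: the number of instructors per arm, the R² between rating and arm, and the share of the effect that runs through the rated content.

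**1. The plan's own sample size.** n per arm = 2(1.960 + 0.842)²/0.50² = 62.8, so 63 by the normal formula and 64 by the t test. Reaching 102 needs attrition of about 1 − 64/102 = 37%. The rate is not stated, so 102 can be neither confirmed nor refuted. The base used below is 64 completers per arm, the number that gives the planned power: 0.50/√(2/64) = 2.83, and Φ(2.83 − 1.96) = 0.81, or about 80%.

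**2. Instructor as a fixed covariate.** If no instructor crosses arms, the arm indicator equals the sum of the yoga-instructor indicators. With an intercept, arm and instructor indicators in the design matrix:

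| Instructors per arm (assumed) | Columns | Rank |
|---|---|---|
| 1 | 3 | 2 |
| 2 | 5 | 4 |
| 3 | 7 | 6 |

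The rank is one short each time, so the arm effect has no unique estimate. Given nesting, this needs no assumption about effect size or correlation.

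**3. One yoga rating per intervention.** The rating is then a linear function of arm. Intercept, arm and rating make 3 columns of rank 2, and again arm is inestimable.

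**4. Ratings that vary within arm.** The model can now be fitted, but the coefficient changes meaning. In a simulation (2,000 runs, 102 per arm, residual SD 1), the rating was arm plus noise, and the outcome effect of −0.50 ran partly or wholly through the rating. Mean adjusted arm coefficient, with rejection rate in brackets:

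| Share through rated content | R² = 0.5 | R² = 0.8 |
|---|---|---|
| None | −0.50 (71%) | −0.49 (35%) |
| Half | −0.25 (24%) | −0.24 (12%) |
| All | 0.00 (5%) | 0.00 (4%) |

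The part of the effect carried by the rated content disappears from the arm coefficient. If that is all of it, the test rejects at about its nominal 5% level. The rejection rates assume all 102 per arm are observed; the average coefficient does not depend on that.

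**5. Loss of precision alone.** Even if none of the effect runs through the rating, the variance of the arm coefficient is multiplied by VIF = 1/(1 − R²). Power = Φ(0.50/√(2·VIF/64) − 1.96):

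| Assumed R² | VIF | Power at 64 per arm |
|---|---|---|
| 0 | 1 | 81% |
| 0.5 | 2 | 52% |
| 0.8 | 5 | 24% |
| 0.9 | 10 | 14% |

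**The case against.** The case on the other side narrows the point in several ways.

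- **The t tests.** Data Analysis names t tests, which take no covariates, and the adjustment sentence can be read as adding adjusted models to unadjusted ones. A reader might infer that the primary pain answer must come out falsely null or uninterpretable. The article does not support that: an unadjusted comparison may well be reported. It does not, however, name the unadjusted test as primary or exempt it from the rule.
- **Coding of instructor.** Mixed models are also named. With a random instructor effect nested in arm, the arm effect is estimable. Inestimability therefore depends on fixed effects, and that choice could reasonably be left to an analysis plan that is not shown. This stands, but it does nothing for the yoga ratings.
- **Nesting.** The article gives different qualifications for the two sets of instructors. It does not say that no one teaches in both arms, nor how many instructors there are. Nesting is a strong inference, not a stated fact.
- **Path b.** The path from change in emotion regulation to later pain is not an arm coefficient, so collinearity with arm does not remove it. It would be wrong to conclude that the whole mediation analysis fails.
- **Credibility.** When this questionnaire is completed is not stated, and Objectives says that the trial wants effects beyond expectancy. It cannot be called a post-allocation variable on this text.
- **Visibility.** Exact collinearity would normally show up as a redundant term at analysis. That is fair for steps 2 and 3, but not for step 4, where the model fits without complaint and answers a different question.

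That the analysis plan may settle details is no full answer, because the difficulty is a rule the article states, not a detail it omits.

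**Conclusion.** The covariate rule is wrong as written for any model that estimates an arm effect. The yoga ratings are the firmer part: by the article's own account they measure the content that distinguishes the arms. Adjusting for them leaves the arm effect either inestimable or stripped of whatever runs through that content. Instructor is a conditional second part, requiring both nesting in arm and fixed effects.

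The size cannot be fixed from the document. The rank results need no R². The fall from about 80% power to about 52%, 24% and 14% is illustrative: it rests on assumed R² values and on 64 completers per arm. A reader might instead start from the roughly 95% power that 102 per arm would give for d = 0.50. That is not the planned power, because 102 already includes an attrition allowance.

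**What to change.** Amend the covariate sentence in Data Analysis as follows:

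- Remove the yoga questionnaire ratings from every model that estimates an arm effect: BPI-SF severity, DERS, path a and the direct path. Use them descriptively or for fidelity, to show that the arms differed in content.
- Include instructor only as a random effect nested in arm.
- Restrict covariates for the arm comparisons to pre-randomisation variables: the baseline value of the outcome, sex (the stratification factor) and cohort.
- Use credibility or expectancy as a main-model covariate only if it was collected before allocation was disclosed. Otherwise report that adjustment as a labelled sensitivity analysis.

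The cost is analysis wording only, with no new data. The Results section plans no interim analyses and places the analysis after final data collection, so the change can be made before outcomes are examined.
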